## Abstract

**Background:**

The onset of puberty and menarche is a specifically vulnerable time for girls, during which they begin to show interest in the opposite sex, while becoming exposed to a myriad of external pressures, including sexual coercion or harassment from boys and men, expectations to marry from their families, and the need to perform well in primary school in order to qualify for secondary school. According to several qualitative studies in Africa, such pressures are exacerbated by girls’ lack of knowledge of their bodies, their rights, and the implications of their decisions, and by their inability to manage puberty and adolescence safely and comfortably with appropriate menstrual health and hygiene management (MHM) products. The evaluation of the Nia Project is one of the first to analyze the individual and combined contributions of sanitary pads and provision of comprehensive reproductive health education on girls’ education and reproductive health outcomes.

**Methods:**

The design for the evaluation of the Nia Project is a longitudinal, cluster-randomized controlled trial consisting of a baseline survey with a cohort of Class 7 girls, a school quality survey, qualitative data collection, school attendance tracking, and an endline survey at the completion of the 18-month intervention period with the same cohort. The study involves 140 public primary schools in three rural sub-counties (Magarini, Kaloleni and Ganze) of Kilifi County in the Coastal area of Kenya. The research sample includes 3489 girls, with about 25 girls per school on average. Before program implementation, the schools were stratified by sub-county and randomized to one of four study arms (35 schools per arm): 1) control, 2) disposable sanitary pads distribution, 2) reproductive health education, and 4) sanitary pad distribution and reproductive health education.

**Discussion:**

The evidence provided will inform program investment and design, and contribute to the literature on the effect of menstrual health-based interventions on girls’ agency, safety and life outcomes.

**Trial registration:**

ISRCTN10894523. Trial Registration Date: August 22, 2017.

**Electronic supplementary material:**

The online version of this article (10.1186/s12978-018-0586-4) contains supplementary material, which is available to authorized users.

## Plain English summary

The time when adolescent girls start to experience puberty and menstruate for the first time contains many risks, including facing sexual harassment and violence from boys and men, their families pressuring them to get married and the expectation to perform well in school. Other studies in Africa confirm that these risks and pressures are made worse by girls’ lack of knowledge of their bodies and their inability to manage puberty and adolescence safely and comfortably with appropriate menstrual products. The evaluation of the Nia Project is one of the first studies to examine the effect of sanitary pads and reproductive health education on girls’ education and reproductive health.

This paper describes the design of the evaluation of the Nia Project, a program that provides girls with sanitary pads and reproductive health education. The study includes a baseline survey of about 3500 girls in Class 7, a school quality survey, qualitative data collection, school attendance tracking, and an endline survey with the same group of girls after the program is completed. The study includes 140 public primary schools in Kilifi County in the coastal area of Kenya. Schools were randomly assigned to one of four program versions: 1) control, 2) disposable sanitary pads distribution, 2) reproductive health education, and 4) disposable sanitary pad distribution and reproductive health education.

The results of this study will shape future program investment and design, and contribute to the understanding of the effects of menstrual health-based interventions on girls’ agency, safety and life outcomes.

## Background

The onset of puberty and menarche is a specifically vulnerable time for girls, during which they begin to show interest in the opposite sex, while becoming exposed to a myriad of external pressures, including sexual coercion or harassment from boys and men, expectations to marry from their families, and the need to perform well in primary school in order to qualify for secondary school [1]. According to several qualitative studies in Africa, such pressures are exacerbated by girls’ lack of knowledge of their bodies, their rights, and the implications of their decisions, and by their inability to manage puberty and adolescence safely and comfortably with appropriate menstrual health and hygiene management (MHM) products [2–8].

Qualitative studies conducted in Kenya have identified several challenges girls face in managing their menstruation, including lack of access to menstrual products and lack of accurate information about menstruation. In a study conducted in Nyanza Province in Western Kenya, girls who participated in focus groups and in-depth interviews reported poverty as a main barrier for proper menstruation management. When families are unable to prioritize buying sanitary pads, girls resort to using cloths, mattress pieces and other materials, but they describe these alternatives as ineffective in preventing leaking of blood onto their clothing [9]. In Siaya County, also in Western Kenya, a qualitative study of young adolescent girls also highlighted the inadequacy of alternatives such as cloths, blankets and mattress pieces and their preference for sanitary pads. Although the most common source of sanitary pads was mothers, some girls reported receiving money from boyfriends to buy pads, often with the expectation that they will have sex with them in return [3].

Both studies found that girls commonly had little or no prior knowledge of menstruation because traditional systems for passing on this knowledge were no longer functional and many mothers did not prepare their daughters for menstruation [3, 9]. Data from focus group discussions in an informal settlement in Nairobi also showed that mothers’ limited knowledge, embarrassment and cultural taboos prevented them from providing their daughters with accurate information on reproductive health, including menstruation [10]. Furthermore, teachers in Siaya most often stated that it was not their role to provide girls with information on menstruation [9].

While several programs have previously been developed to address girls’ MHM needs in Kenya, as well as globally, few have been rigorously evaluated, and where evidence does exist, the results have been mixed. The government of Kenya, in response to girls’ MHM needs has committed to sanitary pad distribution in government schools [11], however, evaluations have shown that the supply chains of sanitary pads to government schools were not reliable, and girls were not assured of equitable pad provision [12].

A 2013 systematic review of the literature identified 14 studies that examined health outcomes such as reproductive tract infections and 11 articles that examined psycho-social outcomes of menstrual hygiene [13]. The authors concluded that while there is some evidence on the impact of MHM on psycho-social outcomes, the impact on health outcomes, specifically reproductive tract infections, is unclear. Furthermore, there is no quantitative evidence on the effects of MHM on reducing school absenteeism. They also noted the lack of rigorous studies showing the impact of MHM on girls’ general health and well-being.

In February 2016, Hennegan and Montgomery published an MHM related systematic review that identified eight studies that fulfilled their criteria: individual or cluster randomized controlled trials (RCT) and non-randomized controlled trials [14]. The purpose of the review was to assess the risk of bias in these studies and synthesize the evidence on the effects of MHM interventions on educational and psychosocial outcomes for women and girls in low and middle income countries. The authors outlined two dominant types of MHM intervention approaches: products, or the provision of physical objects useful for MHM, such as menstrual cups or sanitary pads; and empowerment, or the provision of human and social capital through education and non-tangible benefits. The authors found considerable risk of bias in these studies, mainly selection bias, performance bias, attrition bias, and reporting bias. They were unable to synthesize most results due to differences in interventions and methods and, therefore, concluded that while there are some indications of positive results, insufficient evidence exists for the effectiveness of MHM interventions.

Only one study identified in the review examined the effect of a combined empowerment and products intervention on schooling attendance. The study was conducted in Ghana using a non-randomized cluster-control trial design, with a sample of 120 girls between the ages of 12 and 18 [15]. The three interventions implemented were: 1) provision of pads with puberty education, 2) puberty education alone, and 3) control group (no intervention). School attendance was measured using official school records, triangulated with researcher visits. At the end of the 5-month study period, study investigators observed statistically significant improvements in attendance for both treatment arms, by approximately 5 to 6 days per 65-day term. However, the main limitation of the study was the small sample size and non-randomized design. Dolan and colleagues [16] further reported a significant improvement over time in confidence regarding menstruation management in the study arm that included provision of pads. No statistically significant change in confidence (as measured by shame, self-confidence and insecurity) was observed in the education-only arm. However, as noted by Hennegan and Montgomery [14], these findings should be interpreted with caution because confidence was not measured in the control group, and girls differed on this indicator across sites at baseline.

Due to the lack of clear evidence on the impact of MHM interventions on girls’ education and health, ZanaAfrica received funding in 2015, from the Bill & Melinda Gates Foundation, to implement a holistic solution combining sanitary pads and reproductive health education, including multi-media health education resources. The package of interventions was branded as ‘The Nia Project’, from the Swahili word ‘nia’ which means ‘purpose.’ ZanaAfrica is partnering with Population Council to rigorously evaluate the Nia Project interventions among adolescent girls in Kilifi County, which is located in the Coastal region of Kenya. Kilifi was identified as the study site based on a review of indicators related to education and reproductive health; for example, the low transition rate from primary to secondary school, recorded as 40% in 2010, compared to the national rate of 72% [17]. In addition, Kilifi was ranked 36 out of 47 counties in regards to the Net Enrollment Rate for secondary school for boys and girls, which was only 26% in 2014 [18]. According to the 2014 Kenya Demographic and Health Survey [19], approximately 22% of girls between the ages of 15 and 19 in Kilifi County had begun childbearing, compared to the national average of 18%.

Using a randomized controlled trial (RCT) research design, this evaluation is one of the first to analyze the individual and combined contributions of sanitary pads and provision of comprehensive reproductive health education on girls’ education and reproductive health outcomes. The evidence provided will inform program investment and design, and contribute to the literature on the effect of menstrual health-based interventions on girls’ agency, safety and life outcomes.

The main objective of the research is to answer the following research question: What is the effect of an MHM intervention combining empowerment (reproductive health education) and products (sanitary pads) approaches on girls’ well-being (social, and personal competencies) and education, versus empowerment or products alone? The study was specifically designed to address key limitations of previous studies, which include small sample sizes, inability to determine causation, non-random assignment to study arms, and short follow-up periods.

This paper describes the intervention and research design of the Nia Project.

## Methods/design

The Nia Project interventions are implemented by ZanaAfrica and Plan International, Kenya. Girls enrolled in Class 7 at the start of the 2017 school year are the beneficiaries, receiving interventions over a period of 5 school terms, from May 2017 to December 2018. The Nia Project includes two intervention components: 1) provision of Nia brand disposable sanitary pads, and 2) reproductive health education, including menstrual hygiene management as an extracurricular program for girls enrolled in school.

### Sanitary pads

In 2011, the Kenyan government, through the Ministry of Education, Science and Technology, initiated the Schools’ National Sanitary Towels program to increase girls’ school attendance and participation. The program includes the provision of sanitary pads to school girls and the training of teachers on hygienic usage and disposal of pads (UNESCO Booklet 9 – puberty education and MHM). However, results from a formative assessment conducted in Kilifi to inform the design of the Nia Project indicated that some schools receive inadequate supplies to meet the needs of all female students throughout the year.

For the Nia Project, each girl receives one packet of 10 disposable sanitary pads each month of ZanaAfrica’s Nia Teen brand, for the entire project period. To avoid duplication, schools agreed to only distribute government-issued pads to girls who are not part of the Nia Project, while ZanaAfrica distributes Nia brand disposable sanitary pads to Class 7 girls. Lack of underwear was identified as a barrier to pad usage during the formative assessment. Therefore, project beneficiaries also receive two pairs of underwear at the start of the intervention, and an additional pair at the end of each subsequent term.

### Reproductive health education

Kenyan primary education includes a National Life Skills Education curriculum, which focuses on communication, negotiation and decision-making skills. The curriculum is not comprehensive and has been assessed as being weak in regards to topics such as: power in relationships, reproduction, sexuality and sexual behavior, HIV and sexually transmitted infections (STIs), contraceptives and gender and human rights [20]. Kenya’s 2015 National Adolescent Sexual and Reproductive Health Policy provides the basis for the provision of age-appropriate comprehensive sexuality education (CSE) for in-school adolescents.

The Nia Project reproductive health education intervention is comprised of facilitated health education sessions (FHE) and a health magazine developed by ZanaAfrica. Both components are based on the UNESCO International Technical Guidance on Sexuality Education [21] and designed to incorporate recent evidence on the importance of addressing gender and power in sexuality and HIV education programs [22, 23]. *Nia Yetu,* the curriculum for the FHE sessions, was developed by ZanaAfrica [24] with many elements adapted from the Tuko Pamoja: Adolescent Reproductive Health and Life Skills Curriculum [25] developed by PATH and Population Council as part of the Kenya Adolescent Reproductive Health Program (KARHP). The 25-session curriculum (see Table 1) is delivered by trained facilitators during weekly girls-only health clubs in 2017, and bi-monthly health clubs in 2018, held during time allocated for extra-curricular activities in school.

**Table 1 Tab1:** Nia Yetu Curriculum Topics

Module:	Sessions:	Duration:
1. Welcome to Puberty	1. Getting Started, Values	1:30
	2. Setting Goals	1:05
	3. Adolescence and Puberty	1:35
	4. Menstruation	1:35
	5. Menstrual Health Management	1:30
2. Gender	1. Male and Female Reproductive Systems	1:20
	2. Self Esteem	1:20
	3. Communication	1:20
	4. Introduction to Gender	1:20
	5. Gender Stereotypes	1:20
3. Gender, Power, and Rights	1. Human Rights	1:35
	2. Power Dynamics	1:35
	3. Sexual Violence and Exploitation	1:35
	4. How to Report and Avoid Cases of Sexual Violence	1:10
	5. Being Assertive	1:35
	6. Decision Making	1:10
4. Gender, Power, and Rights	1. Healthy Relationships	1:10
	2. Romantic Relationships	1:10
	3. Sexuality and Behavior	1:15
	4. Teenage Pregnancy	1:15
	5. Sexually Transmitted Infections (STIs) and HIV	1:35
5. Being True to Yourself	1. Resisting Peer Pressure	1:20
	2. Drug Use and Abuse	1:30
	3. Managing Stress, Anger, and Conflict	1:30
	4. Program Wrap Up	1:30

ZanaAfrica’s health magazine, *Nia Teen,* provides content that girls can refer to. It is designed to appeal to adolescent girls and conveys core reproductive health messaging through storytelling using aspirational personal stories, a relatable comic-style story, and activities. *Nia Teen* magazine is distributed at the start of each term for the five-term period. Each issue corresponds directly to the topic covered in each module of the Nia Yetu curriculum that term.

### Cluster randomized study design

The design for the evaluation of the Nia Project is a longitudinal, cluster-randomized controlled trial consisting of a baseline survey with a cohort of Class 7 girls, a school quality survey, qualitative data collection, school attendance tracking, and an endline survey at the completion of the 18-month intervention period with the same cohort. The study involves 140 public primary schools (35 schools per arm) in three rural sub-counties (Magarini, Kaloleni and Ganze) of Kilifi County in the Coastal area of Kenya. Before program implementation, the schools were stratified by sub-county and randomly assigned to one of the following four study arms (See Fig. 1):Control group;Sanitary pad distribution;Reproductive health education; orSanitary pad distribution + reproductive health education.

**Fig. 1 Fig1:**
[figure not shown]
Nia Project study design

### Study sites

The sub-counties and schools were selected in collaboration with the Kilifi County Department of Education, Ministry of Education, Science and Technology. Within the three sub-counties (Magarini, Kaloleni and Ganze), all schools with 25 or more girls in Class 7 were eligible for the study. A total of 215 schools were mapped, and a 1000 m buffer was created around each school. For schools with overlapping boundaries, one school was randomly selected. This resulted in a list of 173 schools with at least 25 girls in Class 6 or in Class 7 in 2016. A listing exercise was conducted to verify enrollment and school type in the first quarter of 2017. Based on this data, 25 schools were excluded because they did not meet the minimum criteria of 25 girls in Class 7, and an additional seven were excluded because they were determined to be boarding schools. Subsequently, one school in Magarini was excluded after it was closed indefinitely by the Department of Education during baseline data collection. This resulted in 140 schools – 44 in Magarini, 50 in Kaloleni and 46 in Ganze.

In schools with 25 girls in Class 7, all girls were included in the research sample. In schools with a larger number of girls, 25 girls were randomly selected for the research sample and five additional girls were selected as alternates. Of the expected 3500 girls, a total of 3489 girls were interviewed as part of the baseline survey. All Class 7 girls, including those who were not in the research sample, are eligible to receive interventions. At the completion of data collection in each sub-county, stakeholder meetings were held and schools within that sub-county were randomly assigned to one of the four study arms through a public lottery.

### Sample size calculations

The sample size was calculated based on power calculations to determine the number of clusters (i.e., schools) and the number of girls needed in each cluster to observe the desired change in the mean days of school missed, according to differences detected in previous studies conducted in Kenya and Ghana [15, 26]. The estimate of the intra-cluster correlation (ICC) and the baseline estimates for childbearing and education were based on a previous menstrual health study conducted in Kenya by Wilson and colleagues [26]. With a sample size of 35 clusters per arm and 20 girls per cluster at endline (25 girls per cluster at baseline, assuming a loss of 20% by endline), the minimum detectable difference between study arms, with power of 0.80 and a significance level of 0.05 is:1.18 mean days of school missed over a 4-week period, with an ICC of 0.173 and a standard deviation of 3.57; anda 13% increase in correct knowledge and attitudes on a reproductive health score from 75 to 85% in intervention arms with no change assumed in the control arm.

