### Analysis plan

The program evaluation of the Nia Project will examine the effect of the average treatment across study arms while identifying the causal mechanisms driving that impact. Using intent-to-treat analysis, all girls in the original sample randomized to study arms will remain part of the study despite non-compliance, protocol deviations, withdrawal, or anything else that happens after randomization. Econometric estimation techniques such as fixed effects estimation will be applied to control for unobserved time invariant individual characteristics. The evaluation will compare the average increase in outcomes of girls in intervention arms to the average increase in outcomes of girls in the control arm. Additional hypotheses will be tested using difference in difference analysis to understand both causal mechanisms among girls who received the interventions and the potential effect of improvements in short-term indicators on longer-term outcomes. The rich dataset will provide an extensive list of variables that can be adjusted for directly in the analysis. The results will be triangulated using qualitative data.

To examine balance across study arms following randomization, multinomial logistic regression models were estimated using each dataset to test for joint orthogonality for a selected list of indicators, comparing each treatment group with the control group. For the school quality dataset, the variables included were: school performance by gender, number of toilets, distribution of pads and availability of pads in stock. The results showed that there were jointly no significant differences between study arms (*p* = .60). For the girls’ dataset, indicators included were: ever repeated a grade, age at starting school, self-efficacy scale, decision-making scale, gender-norms scale, reproductive health knowledge score, ever menstruated, justification of violence, experience of symptoms of reproductive health infections and ever had sex. The results showed that there were jointly no significant differences between study arms (*p* = 0.14).

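### The stated minimum detectable difference of 1.18 days does not follow from its own inputs, which give 1.11 to 1.12 days at 80% power

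*Protocol article*

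**What the plan says.** The Sample size calculations section of the Protocol article puts the full input set and the result in one sentence:

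- Clusters and endline size: "With a sample size of 35 clusters per arm and 20 girls per cluster at endline".
- Origin of the endline size: "25 girls per cluster at baseline, assuming a loss of 20% by endline".
- Error rates: "with power of 0.80 and a significance level of 0.05".
- Result and variability: 1.18 "mean days of school missed over a 4-week period, with an ICC of 0.173 and a standard deviation of 3.57".

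The section on the cluster randomized design confirms equal allocation, with 140 schools in four arms and therefore 35 per arm. The sample size section does not give the sidedness of the test, an adjustment for several comparisons, variation in cluster size, or a correlation between baseline and endline. It does not say whether 3.57 is the standard deviation of a level or of a change.

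**The concern.** School absence is the outcome on which the number of schools and girls was set, so 1.18 days is the trial's headline sizing figure. All the inputs of the usual cluster-adjusted formula stand beside it, and a reader who puts them in gets a different answer. Either the result is wrong, or one of the printed inputs is not the one used, or an allowance was made and not reported. As written, the reader cannot tell which, and the stated power of 80% at 1.18 days is not the power that the stated design has.

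**Working it through.** **Inputs** (Sample size calculations): k = 35 schools per arm, m = 20 girls per school, ICC = 0.173, SD = 3.57 days, power 0.80, alpha 0.05. Two-sided testing and a 1:1 comparison of two arms are assumed.

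**Step 1, attempt to reproduce 1.18.**

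- Check on m: 25 × 0.8 = 20, which is consistent.
- Design effect: 1 + (m − 1) × ICC = 1 + 19 × 0.173 = 4.287.
- Girls per arm: 35 × 20 = 700. Effective number: 700 / 4.287 = 163.3.
- Standard error of the difference: SD × sqrt(2 × 4.287 / 700) = 3.57 × sqrt(0.012249) = 0.3951 days.
- Normal approximation: (1.960 + 0.842) × 0.3951 = 2.802 × 0.3951 = **1.107 days**.
- Noncentral t with 2 × (35 − 1) = 68 df: **1.123 days**.

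The figure of 1.18 is not reproduced. It is too large by 1.18 / 1.107 − 1 = 6.6% (normal) or 1.18 / 1.123 − 1 = 5.1% (t).

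**Step 2, the same gap as power.** 1.18 / 0.3951 = 2.987, and 2.987 − 1.960 = 1.027, which gives a power of 0.848 (normal). The noncentral t gives 0.837.

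**Step 3, the same gap as sample size (normal).** Without clustering, 1.18 days needs 2 × (2.802 × 3.57 / 1.18)² = 143.7 girls per arm. With clustering, this is 143.7 × 4.287 = 616 girls. That is 616 / 20 = 30.8, so about 31 schools per arm rather than 35.

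**Step 4, rounding.** Take the ICC and SD at the top of their rounding ranges, 0.1735 and 3.575. The design effect is 1 + 19 × 0.1735 = 4.2965 and the standard error is 3.575 × sqrt(2 × 4.2965 / 700) = 0.3961. The result is 2.802 × 0.3961 = 1.110. Rounding does not explain the gap.

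**Step 5, standard variants of the calculation.**

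| Variant | Normal | t |
|---|---|---|
| One-sided alpha 0.05 | 0.98 | 0.99 |
| 25 girls per school | 1.085 | 1.101 |
| One school per arm subtracted | 1.123 | 1.140 |
| Design effect as 1 + m × ICC | 1.129 | – |
| 16 girls per school (20% loss taken twice) | 1.133 | 1.150 |
| 28 schools of 25 girls | 1.214 | 1.236 |
| Bonferroni, 2 comparisons | 1.218 | 1.241 |
| Bonferroni, 3 comparisons | 1.278 | 1.306 |

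None gives 1.18.

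**Step 6, what would give 1.18, changing one input at a time.**

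- Power 0.85 instead of 0.80: 1.184 (normal).
- 31 schools per arm (normal, 1.176) or 32 (t, 1.176) instead of 35.
- ICC of about 0.204 (normal) or 0.197 (t) instead of 0.173.
- SD of about 3.81 (normal) or 3.75 (t) instead of 3.57.
- Cluster sizes with a coefficient of variation (CV) of about 0.41 (normal) or 0.36 (t). With CV 0.41 the design effect is 1 + ((1 + 0.41²) × 20 − 1) × 0.173 = 4.87.

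The first four contradict a printed input. The fifth adds one that is not printed.

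**The case against.** The best defence is that a condensed article may omit a legitimate allowance. Two candidates are ordinary: planning at 85% power, and allowing for unequal school sizes at endline after 20% loss. Some variation in size is likely, and neither possibility can be excluded. But the text says 0.80, so the first contradicts it. The second needs a large spread: a CV of 0.36–0.41 on a mean of 20 is a standard deviation of about 7 to 8 girls per school, although at most 25 girls per school were to be sampled. In either case the allowance has to be stated, because the sentence presents the result as following from the listed inputs.

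It is also fair to say that the gap is small, 0.06 to 0.07 days per 4 weeks, and on the safe side. That stands, and it limits the weight of the point.

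Three stronger readings may suggest themselves, and the document does not support them.

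- *The trial is too small.* The opposite holds on the stated inputs, since 1.18 days is detectable with more than 80% power.
- *1.18 is the wrong figure for the planned analysis.* The Analysis plan will "compare the average increase in outcomes of girls in intervention arms to the average increase in outcomes of girls in the control arm", and a reader might infer that 1.18 cannot be the detectable difference of such a comparison of changes. That cannot be shown. If 3.57 is the SD at both waves and one correlation r applies at school and girl level (both assumptions), the normal figure is 1.107 × sqrt(2(1 − r)): 1.40 at r = 0.2, 1.31 at r = 0.3 and 1.11 at r = 0.5. It equals 1.18 near r = 0.43 (0.45 by t). No r is given, and 3.57 might itself be the SD of a change.
- *A null attendance result could not be interpreted.* What a null result excludes is set by the confidence interval, with the observed variance and clustering, and not by the planning figure.

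**Conclusion.** Wrong as written, but minor. The stated inputs give a minimum detectable difference of 1.11 days (normal) or 1.12 days (t, 68 df) at 80% power, against 1.18 printed. At 1.18 days the power is about 84–85%. The figure is 5–7% too large, in the conservative direction, so neither the number of schools nor the number of girls is called into question. The result rests on a two-sided 0.05 test of one arm against another with equal cluster sizes. A one-sided test would widen the gap. The conclusion is confined to the disagreement between the inputs and the result in the sample size sentence.

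**What to change.** Correct the sentence in Sample size calculations in one of three ways:

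1. Keep the inputs and restate the result as 1.11 days (normal approximation) or 1.12 days (t, 68 df), saying which method was used and that the test is two-sided.
2. Keep 1.18 days and state the power as about 85% (normal) or 84% (t).
3. If 1.18 came from an allowance that is not printed, such as unequal cluster sizes or a different power, name it and give its value, so that the figure can be reproduced.

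The original calculation file should settle which applies. The cost is a change of wording only, with no change to the sample, the design or the analysis.
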